**STUDY VARIABLES**

| **Event** | **Screening** | **1-2 month(s)**  **post-transplantation** | **12 months**  **post-transplantation** | **Annual**  **for 5 years** |
| --- | --- | --- | --- | --- |
| **Criteria** **for**  **inclusion/exclusion** | X |  |  |  |
| **Informed**  **consent** | X |  |  |  |
| **Laboratory test** | X | X |  |  |
| **Echocardiogram** | X | X | X |  |
| **Medication** | X | X | X |  |
| **Functional invasive coronary test** |  | X | X |  |
| **Events during**  **follow-up** |  |  | X | X |

**ABBREVIATIONS**

**AAR:** acute allograft rejection

**ACR:** acute cellular rejection

**CFR:** coronary flow reserve

**EMB:** endomyocardial biopsy

**FFR:** fractional flow reserve

**HT:** heart transplant

**IMR:** index of microvascular resistance

**IST:** immunosuppressive therapy

**MVD:** microvascular dysfunction

**Pa:** aortic pressure

**Pah:** aortic pressure at hyperemia

**Pd:** distal coronary pressure

**Pdh:** distal coronary pressure at hyperemia

**RFR:** resting full-cycle ratio

**Tmnh:** mean transit time at hyperemia

**Tmnr:** mean transit time at rest

**INTRODUCTION AND RATIONALE**

Heart transplant (HT) is considered the treatment of choice for patients with advanced heart failure refractory to medical treatment or devices.

Acute allograft rejection (AAR) is the main cause of mortality and re-transplantation,  particularly during the first year. The immune response is classified into acute cellular rejection (ACR) when mediated by T lymphocytes, and humoral rejection when involving B lymphocytes and antibody production. Of note, up to 20% of HT patients experience at least one episode of ACR during the first year post-transplantation (1). Advances in immunosuppressive therapy (IST), donor heart evaluation, surgical techniques and post-HT care have led to a reduction in ACR, improving survival over time (2-3). Post-transplant IST includes three basic components: a calcineurin inhibitor (currently preferred Tacrolimus), an antiproliferative agent (mycophenolate mofetil), and steroids. On the other hand, proliferation signal inhibitor (mTOR) drugs (everolimus and sirolimus) are primarily used for CAV (3-4). CAV is the main cause of mortality after the first year of transplantation. It is characterized by diffuse intimal thickening affecting both coronary epicardial and microcirculation (2,4).

The vast majority of ACR occur asymptomatically with normal ventricular function, and thus being detected by endomyocardial biopsy (EMB). EBM is the "gold standard" to guide post-HT treatment (4). The graduation of the RAC is detailed in the 2005 review of the ISHLT (5). Due to intra- and inter-observer variabilities in determining different degrees of slight-moderate rejection, an update was published in the 2010 document. In the International Society of Heart and Lung Transplantation (ISHLT) guidelines, EMB was made a IIaC recommendation for the detection of rejection (2). EMB is repeatedly performed during the first year after HT and is associated with complications that, despite infrequent, can be potentially serious, such is the case of cardiac perforation. Moreover, EMB diagnostic yield is wide, with a high variability between observers and a non-negligible rate of false positives and negatives (6).

In order to avoid the inconveniences of EMB, non-invasive techniques have been studied to detect rejection, with some positive results. However, none of these techniques has been able to replace EMB (7).

Various studies have demonstrated the association between ACR, microvascular dysfunction (MVD) and cardiac allograft vasculopathy (CAV) (8). IMR is a quantitative and specific index for coronary microcirculation (9-10).  An increased IMR in the graft has been associated with higher all-cause mortality and adverse cardiac events regardless of epicardial vasculopathy (11). Several IMR cut-off (from 15 to >25) have been associated with ACR within the first year after HT. Patients in whom IMR decreases or does not change one year after HT have a higher event-free rate than those patients in whom the IMR increases (12-13). However, no study has evaluated IMR impact on post-HT management. In presence of a low IMR value, EMB could be performed less frequently; on the contrary, if the IMR value is high, immunosuppression therapy could be modified by an earlier administration of mTor-inhibiting drugs or prescribing calcium antagonists, which are known to improve microvascular function.

Our aim will be to assess if post-HT patient management may be safely modified based on IMR value.

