## 3.4. Outcomes

- The **primary outcome** of the study is to evaluate IMR values and number of EMB performed in the first year after HT: Depending on IMR values obtained in the first three months, clinical status and the other complementary tests the physician will be able to modify the number of biopsies established in each center protocol.If the IMR is less than 15, the number of biopsies could be reduced or kept the same. If the IMR is 15 or greater,number of biopsies would be performed as usual per protocol.

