**- Secondary outcomes:**

-IMR variation between first three months after HT and one year: Comparison between the values of index of microvascular resistance (IMR) measured by bolus thermodilution technique between the first and 3rd month after HT and one year in the invasive physiological study. IMR may be expressed as mmHg·s.

-Acute cellular rejection: A ≥2R degree according to the 2010 ISHLT system. Two or more focal infiltration points associated with myocyte injury in EMB. Diffuse infiltration with multi-focal myocyte injury with/without oedema, hemorrhage or vasculitis.Time frame: One year.

-Cardiac allograft vasculopathy: Accelerated fibroproliferative process characterized by diffuse, concentric and longitudinal thickening of the intima of the vascular tree of the graft, affecting everything from the major epicardial arteries to the coronary microvasculature.Time frame: 5 years.

-Cardiovascular mortality:Caused by cardiovascular disease or unknown death. Time frame: 5 years.

-Heart failure: Diastolic or systolic heart failure after heart transplant. Time Frame: Five years.

-Inmunosupressive therapy: Changes in any of the inmunosuppresive agents pre-established in each center heart transplant protocol. Time Frame: Five years

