**STUDY DESIGN**

**ENDPOINTS**

*The main objective* of the study is to evaluate IMR values and number of EMB performed in the first year after HT.

S*econdary endpoints* are:

- Analyze the relationship between ACR and IMR.
- Analyze the relationship between CV mortality and IMR.
- Analyze the relationship between CAV and IMR.
- Analyze the relationship between the variation IMR value in the first two months and one year, and cardiovascular events.
- Analyze the relationship between the combined endpoint of ACR, heart failure, re-transplantation, CV mortality and IMR.
- Assessment of immunosuppressive therapy after IMR results.

All endpoints will be evaluated at 1 year, and annually thereafter for up to 5 years.

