***Definition of events***

- **Acute cellular rejection (ACR**): A ≥2R degree according to the 2010 ISHLT system. Two or more focal infiltration points associated with myocyte injury in EMB. Diffuse infiltration with multi-focal myocyte injury with/without oedema, hemorrhage or vasculitis (2).
- **Cardiovascular mortality:** Caused by cardiovascular disease or unknown death.
- **Cardiac allograft vasculopathy:** Accelerated fibroproliferative process characterized by diffuse, concentric and longitudinal thickening of the intima of the vascular tree of the graft, affecting everything from the major epicardial arteries to the coronary microvasculature (2).
- **Combined endpoint:** ACR, heart failure, re-transplantation and cardiovascular mortality.
- **Cardiac catheterization complications:** any complication (major or minor) related to the performance of EMB, coronary angiography and functional study.

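### Acute cellular rejection depends on a biopsy grade that the protocol calls observer-variable, and nothing keeps the IMR from whoever does the grading

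*Protocol*

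**What the plan says.** - **Event.** Protocol section 3.4 (secondary outcomes) and the later Definition of events both define ACR by biopsy grade alone: "A ≥2R degree according to the 2010 ISHLT system". No other route to the event is given.
- **Use of the event.** The Endpoints section lists the aim "Analyze the relationship between ACR and IMR", and section 2.2 has the same objective. ACR is also the first component of the combined endpoint: "ACR, heart failure, re-transplantation and cardiovascular mortality".
- **Reliability of the grade.** The Introduction and Rationale explains the 2010 update of the grading document with the words "Due to intra- and inter-observer variabilities in determining different degrees of slight-moderate rejection". A few sentences later it says, in the present tense, that "EMB diagnostic yield is wide, with a high variability between observers and a non-negligible rate of false positives and negatives".
- **Who knows the IMR.** Under section 3.4, depending on the IMR and other findings, "the physician will be able to modify the number of biopsies established in each center protocol". Biopsies and immunosuppressive therapy likewise leaves management to the physician, with the IMR in hand.
- **Masking.** The trial summary (section 1) gives None, and section 3.9.1 (Blinding mechanism) carries no text. Section 5.3.3 names a coordinating centre and a data management team. No section says who grades the biopsies, provides for central reading or adjudication, or withholds the IMR from the reader.

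**The concern.** Treating physicians must know the IMR, because the study is about how they use it. The person grading the slide does not need it. If that person has it, grading error may differ between the IMR groups.

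The protocol also supplies a direction for such an error. Section 2.1 says that patients with an IMR of 15 or more have a higher risk of rejection, and the Introduction and Rationale links several IMR cut-offs to ACR. A reader who knows the value and the expectation could resolve a doubtful slide upward when the IMR is high and downward when it is low. The event definition turns partly on the number of foci with myocyte injury, so a single focus can decide it.

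Grading error that is the same in both groups usually dilutes an association. Error that depends on the IMR can create or inflate one. At stake are the ACR–IMR relationship, the combined endpoint, and the stated aim of learning whether management can be safely modified on the IMR. The introduction says that most ACR is asymptomatic and found by biopsy, so the grade is the main rejection evidence for that aim. The mechanism acts slide by slide and would operate even if both groups had the same number of biopsies.

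**Working it through.** **What the documents fix.** Patients with ACR before the physiological study are excluded (section 3.2). Every counted ACR event therefore follows the exclusion check at that study, and the IMR can already be known when the slide is read. IMR is split at 15. The protocol states no reading-error rate, no borderline share, no group sizes and no target effect for ACR, so there is no figure of its own to reproduce. All inputs below are assumptions unless a source is named.

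**Check 1: risk ratio created by grading alone.** Assume four biopsies per patient after the IMR in both groups, and a 4% chance of 2R or higher per biopsy when read without the IMR. Let *b* be the share of slides that are borderline (15–30%), *u* the share of those moved up in the high-IMR group (5–10%), *d* the share of true 2R readings moved down in the low-IMR group (0, or 5–10%), and *k* the share of readings made with the IMR known.

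- High group: p = 0.04 + k·b·u
- Low group: p = 0.04·(1 − k·d)
- One-year ACR = 1 − (1 − p)^4

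| Case | p high | p low | ACR high | ACR low | Risk ratio |
|---|---|---|---|---|---|
| k = 0 | 0.040 | 0.040 | 15.1% | 15.1% | 1.00 |
| k = 20%, upgrading, low end | 0.0415 | 0.040 | 15.6% | 15.1% | 1.04 |
| k = 20%, upgrading, high end | 0.046 | 0.040 | 17.2% | 15.1% | 1.14 |
| k = 100%, upgrading, low end | 0.0475 | 0.040 | 17.7% | 15.1% | 1.17 |
| k = 100%, upgrading, high end | 0.070 | 0.040 | 25.2% | 15.1% | 1.67 |
| k = 100%, with downgrading, low end | 0.0475 | 0.038 | 17.7% | 14.4% | 1.23 |
| k = 100%, with downgrading, high end | 0.070 | 0.036 | 25.2% | 13.6% | 1.85 |

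Among 50 high-IMR patients, 17.7% against 15.1% is about one extra patient and 25.2% against 15.1% about five.

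**Check 2: false-positive rate.** Inputs from the protocol are 100 patients (section 3.12.1), a two-sided 0.05 chi-square test (same section) and 20% ACR, the upper figure in the introduction. Assume no true relationship and a 50/50 split. The exact binomial rejection probability is:

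- 20% v 20%: 5.2%
- 22.5% v 17.5% (risk ratio 1.29): 9.8%
- 25% v 15% (risk ratio 1.67): 24.4%

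The 25% v 15% case is a net shift of 0.05 × 50 = 2.5 patients in each group. With 30 high-IMR and 70 low-IMR patients it gives 24.0%, and with 70 and 30 it gives 17.7%.

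**Check 3: same error in both groups.** With sensitivity 0.80 and specificity 0.95 in both, the graded rate is 0.20 × 0.80 + 0.80 × 0.05 = 20% in each, so the risk ratio is 1.00 and the false-positive rate stays at 5.2%. With 0.90 and 0.93 in the high group and 0.70 and 0.97 in the low group, the rates are 23.6% and 16.4%, a risk ratio of 1.44 and a false-positive rate of 14.9%. The dependence on IMR does the damage, not imperfect reading as such.

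**The case against.** The strongest reply is that the mechanism rests on silence. The protocol does not mention a pathologist or say that the IMR reaches one. Masking given as None describes a single-group, non-randomized study and says nothing specific about slide reading. This stands in part: a local reader and a leak of the IMR are both inferences, and the range must include a risk ratio of 1.0. It does not remove the point, because what pathology is told is a matter of study conduct. A later analysis plan cannot undo a grade already made with the IMR known.

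A reader might infer that the protocol admits disagreement at exactly the 2R boundary under the grading it uses. It does not. The sentence on slight-moderate rejection explains why the 2010 update was issued, and the event uses the 2010 system. Nor does the protocol label 2R as moderate, natural as that reading is. The later, general sentence on biopsy variability carries the point.

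The top of the range is also demanding. Moving p from 0.04 to 0.07 means that 0.03/0.07 = 43% of 2R calls in the high-IMR group would be false. It is an upper illustration, not an expectation.

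Finally, the primary outcome (IMR values and number of biopsies) does not use the grade directly. That stands.

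**Conclusion.** The point holds in a limited form and merits a modest change. A secondary outcome and the combined endpoint depend on a grade that the protocol itself describes as variable between observers, and no safeguard keeps the IMR from the reader. If readers know the IMR, a spurious or inflated relationship with ACR can arise at equal biopsy numbers. The documents do not give its size. Under the stated assumptions the false risk ratio lies between 1.0 (no reader knows the IMR) and about 1.7 (all do), or about 1.9 with downgrading in the low-IMR group.

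Two stronger conclusions are not supported. One is that ACR is the most frequent component of the combined endpoint: the protocol gives no rates for the other components. The other is that the overall ACR–IMR result must be biased in favour of IMR. The direction described applies to this mechanism only. The protocol also allows intensified immunosuppression at an IMR of 15 or more, which could lower ACR there, and fewer biopsies below 15, which could lower its detection there.

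**What to change.** In Definition of events and section 3.9.1, state that biopsy requests for study patients omit IMR, CFR and IMR group, and that ACR is graded without them. Add one yes/no field in REDCap for whether the reader knew the IMR. Recruitment is already open (section 1), so complete the field for biopsies already graded as well. Repeat the ACR–IMR analysis excluding grades made with the IMR known.

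Treating physicians keep the IMR, and no second or central reading is needed. The cost is an instruction to eight centres, one data field and slightly less clinical context for pathology. Grades already made with the IMR known cannot be made masked, but they can be identified and set aside in the repeated analysis. The change does not address the separate bias from unequal biopsy numbers by IMR group.

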**STUDY DESIGN**

**ENDPOINTS**

*The main objective* of the study is to evaluate IMR values and number of EMB performed in the first year after HT.

S*econdary endpoints* are:

- Analyze the relationship between ACR and IMR.
- Analyze the relationship between CV mortality and IMR.
- Analyze the relationship between CAV and IMR.
- Analyze the relationship between the variation IMR value in the first two months and one year, and cardiovascular events.
- Analyze the relationship between the combined endpoint of ACR, heart failure, re-transplantation, CV mortality and IMR.
- Assessment of immunosuppressive therapy after IMR results.

All endpoints will be evaluated at 1 year, and annually thereafter for up to 5 years.

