## 3.12. Statistical methods

### 3.12.1. Outcomes

The characteristics of the study population will be summarized through standard descriptive statistics. Continuous variables will be expressed as mean (± standard deviation) or median [interquartile range (IQR)], as appropriate. Discrete variables will be presented as absolute numbers and percentages. For the comparison of means, the Student's t test for independent measures or the non-parametric Mann-Whitney U test (in the case of dichotomous qualitative variables) and the ANOVA or non-parametric Kruskal test will be used as a hypothesis test. Wallis (in the case of non-dichotomous qualitative variables). For the bivariate analysis of the qualitative variables, the Chi-square test or Fisher's exact test will be used. Events will be compared between groups by using Kaplan-Meier curves. Cox regression analysis will be performed to adjust for confounding factors and to evaluate independent predictors of clinical events. A two-tailed p-value of 0.05 will be considered statistically significant. All statistical analyses will be performed by SPSS software version 20.

In 2023, around 325 heart transplants were performed in Spain (3). Given a median of 10-15 HT per center and considering that eight centers that routinely perform invasive coronary physiology are participating, data will be analyzed when 100 patients have completed first year follow-up.

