***Procedure***

**Invasive physiological evaluation of the coronary microcirculation**

Patients included will undergo a coronary angiography between the first and third month after HT.  This coronary angiography is part of the follow-up protocol in most of the centers. Assessment of IMR, coronary flow reserve (CFR) and fractional flow reserve (FFR) will be performed using the standard technique (9-10,14).

The left anterior descending coronary artery will be evaluated in all patients. Circumflex or right coronary artery could be additionally evaluated at operator’s discretion. An intracoronary pressure and temperature sensor-tipped guidewire (Pressure Wire TM X guide- wire 0.014’, Abbott, IL, USA) will be used to perform the measurements. The tip pressure sensor will be advanced into the mid-to-distal portion of the evaluated vessel. Baseline aortic pressure (Pa) and distal intracoronary pressure (Pd) will be obtained to calculate the resting index Pd/Pa. To measure the mean transit time (Tmn) under basal conditions, intracoronary administration of 3 mL of room-temperature saline will be manually injected three times in succession (3 mL/s). Then maximal hyperemia will be induced using adenosine iv (140 to 180 mg/kg/min) and three additional intracoronary room temperature saline boluses of 3 ml will be administered to determine the mean transit time at hyperemia (Tmnh). Finally, fractional flow reserve (FFR), coronary flow reserve (CFR) and IMR will be calculated using the software Coroventis Coroflow (*Coroventis Abbott, Uppsala, Sweden)*.

- FFR is defined as the ratio of maximal coronary blood flow in a diseased artery to maximal coronary blood flow in the same artery without stenosis. FFR is a surrogate marker of inducible myocardial ischemia caused by epicardial coronary stenosis.

- CFR is the ratio of hyperemic to baseline flow and is a marker of the integrity of both epicardial and microvascular coronary circulation. Therefore, CFR represents the microvascular status when there is no significant epicardial disease.

- IMR is the minimum achievable coronary microcirculatory resistance and a more specific marker of the coronary microcirculation. It is calculated as the ratio of distal coronary pressure to coronary flow at hyperemia and presented in units (mmHg.s).

The physiological study assessing IMR, CFR and FFR will be repeated again one year after HT.

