***Statistical analysis***

The characteristics of the study population will be summarized through standard descriptive statistics. Continuous variables will be expressed as mean (± standard deviation) or median [interquartile range (IQR)], as appropriate. Discrete variables will be presented as absolute numbers and percentages. For the comparison of means, the Student's t test for independent measures or the non-parametric Mann-Whitney U test (in the case of dichotomous qualitative variables) and the ANOVA or non-parametric Kruskal test will be used as a hypothesis test. Wallis (in the case of non-dichotomous qualitative variables). For the bivariate analysis of the qualitative variables, the Chi-square test or Fisher's exact test will be used. Events will be compared between groups by using Kaplan-Meier curves. Cox regression analysis will be performed to adjust for confounding factors and to evaluate independent predictors of clinical events. A two-tailed p-value of 0.05 will be considered statistically significant. All statistical analyses will be performed by SPSS software.

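### IMR change is known only at the 12-month study, so it cannot predict events at the 1-year evaluation, and later evaluations need a month-12 start

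*Protocol*

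**What the plan says.** All references are to the Protocol.

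- **Endpoint.** The ENDPOINTS section lists: "Analyze the relationship between the variation IMR value in the first two months and one year, and cardiovascular events". Section 2.2 carries the same objective.
- **First IMR.** "Patients included will undergo a coronary angiography between the first and third month after HT". The endpoint itself speaks of the first two months. The two windows need reconciling, but the argument below holds under either.
- **Second IMR.** "The physiological study assessing IMR, CFR and FFR will be repeated again one year after HT". The study-variables schedule also places the repeat functional test at 12 months.
- **When endpoints are evaluated.** "All endpoints will be evaluated at 1 year, and annually thereafter for up to 5 years".
- **Analysis trigger (section 3.12.1).** "data will be analyzed when 100 patients have completed first year follow-up".
- **Methods.** "Events will be compared between groups by using Kaplan-Meier curves", and "Cox regression analysis will be performed to adjust for confounding factors and to evaluate independent predictors of clinical events". Neither sentence gives a time origin, a landmark or a time-dependent exposure. Section 3.12.3 marks analysis population and missing data as not applicable.
- **Exclusions.** Cellular rejection is an exclusion only if it occurs before the physiological assessment. Rejection between the first study and month 12 is therefore not removed.

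**The concern.** IMR change needs two measurements, and the second is made at month 12. An event in month 6 happens before the exposure exists. If such an event itself raises the 12-month IMR, an analysis that counts it will show rising IMR associated with events although the order is the reverse. The protocol's rationale makes this plausible, because it links rejection with microvascular dysfunction.

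The intended reading is prognostic. The rationale cites earlier work in which patients whose IMR fell or stayed level had a better event-free rate, and the Cox model is meant to find independent predictors. A result at 1 year could therefore be reported as prediction when it cannot be.

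There is also a selection issue. Patients who die or are re-transplanted before month 12 have no IMR change for the original graft, and the introduction places rejection-related death and re-transplantation particularly in the first year.

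**Working it through.** **1. The plan's own figure.** The 100 patients are a feasibility count: 8 centres × 10 to 15 transplants = 80 to 120, midpoint 100. No event number or effect size stands behind it, so there is no power calculation to reproduce.

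**2. The 1-year evaluation.** The exposure is known at month 12 and events are counted up to month 12. By definition, 100% of them precede or coincide with the exposure. For scale, the rationale says that "up to 20% of HT patients experience at least one episode of ACR during the first year post-transplantation". That is up to about 20 patients per 100, if rejection counts as a cardiovascular event.

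**3. The planned data cut.** Patients recruited early will by then have follow-up beyond month 12.

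- Inputs: first-year risk p = 0.20 (the protocol's upper figure for rejection, used here as the event risk by assumption); hazard h = −ln(1 − p) = 0.2231; hazard after month 12 = r·h (r assumed); uniform accrual over A years, so follow-up beyond month 12 is uniform on 0 to A. Deaths are ignored in this step.
- First events after month 12: (1 − p) × [1 − (1 − e^(−rhA))/(rhA)].
- A = 2 (the stated recruitment period), r = 1: rhA = 0.4463; (1 − 0.640)/0.4463 = 0.8067; 0.80 × 0.1933 = 0.155. Share before month 12 = 0.20/0.355 = **56%**.
- A = 1, r = 0.25: rhA = 0.0558; the bracket is 1 − 0.9726 = 0.0274; 0.80 × 0.0274 = 0.022. Share = 0.20/0.222 = **90%**.
- Over assumed first-year risks of 10% to 30%, the share runs from 53% to 91%.

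**4. Effect of reverse causation on a Cox model timed from transplant.** 1,500 simulated studies per setting, with 100 patients, 20% yearly event risk, 5% yearly death and two-year accrual. IMR rise is compared with no rise among patients alive at month 12, and IMR change has no true prognostic effect. The only link is an assumed shift in IMR change after an event before month 12.

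| Assumed shift (SD) | From transplant: HR | Type I error | From month 12: HR | Type I error |
|---|---|---|---|---|
| 0 | 1.00 | 4.4% | 0.98 | 3.7% |
| 0.25 | 1.23 | 7.5% | 0.98 | 3.7% |
| 0.5 | 1.50 | 18% | 0.98 | 3.7% |
| 1.0 | 2.14 | 50% | 0.98 | 3.7% |

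The month-12 columns do not vary because that analysis drops every patient with an earlier event, and those are the only patients whose value was shifted. Mean first events fall from 33.1 to 14.3.

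**5. Deaths before month 12.** Everyone with an IMR change, rising or not, was alive at month 12. In a Cox model for death among these patients no death occurs before month 12, so those months add no term to the partial likelihood. Subtracting 12 months from every time leaves the order of deaths and the risk sets unchanged, so the hazard ratio is the same as from a month-12 start.

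Kaplan-Meier is different, because a curve drawn from transplant stays at 100% through year one. The protocol gives no rate of death or re-transplantation before month 12. If it is 5% to 20% (assumption), 5 to 20 of 100 patients have no value. The curve then shows 100% where 95% to 80% remain alive on the original graft, an overstatement of 5 to 20 percentage points at month 12.

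**The case against.** The strongest reply is that the protocol does not prescribe the faulty analysis. Its methods paragraph is generic, gives no time origin, and never says that IMR change enters a Cox model from transplant. Such detail often sits in an SAP, which is not at hand. Section 3.4 and the summary table describe IMR variation only as a comparison of two values, which suits descriptive reporting at 1 year. This stands as far as it goes: analysis from transplant is an unguarded default, not an instruction. It does not rescue the 1-year evaluation, which the protocol itself fixes and for which no SAP can supply follow-up after the exposure.

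A reader might go further than the documents allow in three ways.

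- **That the mortality comparison suffers immortal-time bias.** It does not, as step 5 shows. The guaranteed survival is the same in both groups. Absolute survival and generalisability are affected.
- **That all events precede the exposure throughout the study.** This is true only at 1 year. Annual follow-up to 5 years yields events that properly come after it.
- **That rejection is certainly among the events.** The protocol's event definitions do not define cardiovascular events, and rejection is listed as a separate endpoint. If it is counted, section 3.4 gives it a one-year time frame, which would put all of it before the exposure. That frame conflicts with the five-year evaluation in the ENDPOINTS section.

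**Conclusion.** The point holds in limited form, for one secondary endpoint. The primary endpoint is untouched.

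- **Certain from the text:** at the 1-year evaluation no prognostic relation between IMR change and events can be estimated, and patients lost to death or re-transplantation before month 12 have no value for the original graft.
- **Conditional:** at later evaluations, counting earlier non-fatal events risks reverse causation. The 56% to 90% share rests on a 20% risk borrowed from rejection and on assumed accrual and hazards. The hazard ratios of 1.23 to 2.14 rest wholly on the assumed shifts. With no shift there is no bias in this model, so these figures are illustrative.
- **Not supported:** a biased hazard ratio for death, or an endpoint beyond repair. Events after month 12 can validly be related to IMR change.

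**What to change.** For this endpoint, state in the protocol that:

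1. time starts at the date of the 12-month physiology study;
2. patients alive at that date with both IMR values are included, and re-transplanted patients are handled by a stated rule;
3. only later events count, with patients who had an earlier event either excluded or kept with adjustment for it (only exclusion was simulated above);
4. the analysis uses the annual follow-up data, and the 1-year evaluation reports IMR change descriptively, with the number lacking a second IMR and the reasons;
5. the events that count as cardiovascular are listed, including whether rejection is one.

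Analysing first-year rejection as a predictor of IMR change would be a new, optional objective and is not needed for the repair.

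The cost is wording, with no new data collection. The result comes later and on fewer events: about 14 instead of 33 first events at the first data cut under the step 4 assumptions, if patients with earlier events are excluded.
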